## Abstract

**Objectives:** The cervical cancer screening coverage remains moderate (60%) in France. The aim of the study is to evaluate the efficacy of two experimental invitation strategies (offer of urine or vaginal self-sampling kits) to reach under-screened populations and compare them with the current invitation strategy in rural departments (low medical density and low participation rate) in France.

**Methods:** The study is a randomised controlled trial with three arms: a control arm (conventional invitation letter) and two experimental arms (mailing of a urine or vaginal self-sampling kit). The target population includes women aged 30–65 years, who had no screening test recorded since more than 4 years and who did not respond to an invitation letter within 12 months before. The primary outcome measure is the participation rate in each arm. A team of psychologists will also investigate attitudes and experiences by semi-structured/focus-group interviews with voluntary CapU4 participants and with health professionals.

**Result and conclusion:** CapU4 will identify effective strategies to reach women not responding to current screening invitations and will generate information about acceptance of self-sampling among women and health professionals.

## Introduction

In 2018, cervical cancer (CC) ranked fourth in terms of cancer incidence and was the fourth most frequent cause of cancer-related mortality among women worldwide [1]. In France, it was the 12th most common cancer with 2,900 new cases per year and the 12th most common cancer for mortality (about 1,100 deaths per year) [2]. In Europe, CC screening over the last 50 years has significantly reduced the incidence and mortality associated with CC [3, 4]. This decrease is attributed to the widespread use of CC screening with a Pap smear [5]. At this time, despite the campaigns and letters of encouragement to have the cervical sample, the screening coverage remains moderate (around 60%) in France [2]. Various barriers to women’s participation have already been examined in previous studies: fear for the speculum examination, discomfort with the gynaecological examination, a previous negative experience, unequal access to gynaecological follow-up, time constraints, fear of the result and treatments and low perceived risk of CC [6–8].

The third French Cancer Plan (2014–2019) aimed to extend organised cervical cancer screening piloted in 12 departments including the Maine-et-Loire. The long-term objective was to reduce incidence and mortality by 30% in 10 years, by achieving 80% screening coverage and by making screening more accessible to vulnerable populations (economic precariousness because they benefit from supplementary universal health care coverage, medically desertified places with unequal access to gynaecological follow-up or the lack of a gynaecologist or family physician, etc.) [9]. In July 2019, the French National Authority for Health (Haute Autorité de Santé, HAS) proposed a new national strategy involving Human Papillomavirus (HPV)-based screening for women aged 30–65 years at an interval of 5 years, with the option of vaginal self-sampling as part of a reminder. For women aged 25 to 29, screening is still based on cytological examination of a Pap smear every 3 years after two consecutive annual smears (previous recommendation for all women aged 25–65 years) [10].

Since 2020, the organised screening has been extended nationally. It includes sending invitations to have a cervical specimen taken by a health professional sent to women who have not been screened for more than 3 years, with reminders sent again if no response registered 12 months after the first invitation, and a follow-up of all women for whose screening test result is abnormal (pathological smear or positive HPV test) [11, 12].

Additional interventions are being considered to increase screening coverage, such as offering self-sampling kits to non-responders. Systematic reviews have shown that HPV DNA testing using an appropriate PCR-based assay on a self-taken vaginal sample is as accurate in detecting cervical precancer as HPV testing on a clinician-taken sample [13]. Moreover, meta-analyses of randomised participation trials have demonstrated that sending self-sampling kits is more effective in reaching under-screened populations than conventional invitations to have a screening specimen taken by a clinician. However, the absolute participation rates are highly variable among studies [14]. HPV testing can also be performed on first-void urine [15], which is less invasive and might be even more acceptable than vaginal self-sampling for women reluctant to undergo gynaecologic examinations. The clinical accuracy of HPV testing on urine and on vaginal samples was investigated in the VALHUDES trial (VALidation of HUman papillomavirus assays and collection DEvices for Self-samples and urine samples) [16]. However, no data exist today indicating that sending urine collection kits may be more effective than sending vaginal self-collection kits or conventional invitations. HPV testing on urine is currently only proposed in research protocols [17–19]. Between 2016 and 2018, the CapU3 study sent approximately 13,000 urine collection kits to women living in the Department of Maine-et-Loire, aged 35–65 years, who did not have screening record since 7 years ago or longer [20]. In the routine screening programme, low response rates were observed among women who often remain indifferent to re-invitations sent by simple mail. In the CapU3 study, we noted higher responses (participation rate of 15.4%) when urine collection kits were sent to non-participants in medically underserved areas [20]. However, the CapU3 trial did not include a comparison arm impeding to demonstrate evidence of comparative efficacy.

This article describes the protocol for a randomised trial in which we will assess the efficacy of two experimental invitation strategies (including self-sampling) to reach under-screened populations and compare them with the current invitation strategy in three rural departments (low medical density and low rate of smear participation) in France.

## Methods

### Objectives

The main objective of CapU4 study is to evaluate the effectiveness of two experimental invitation strategies (urine or vaginal self-sampling) to reach under-screened populations and compare them to the current invitation strategy in rural departments in France, and to improve the response rate among women aged 30–65 years (not screened over a period longer than the recommended screening interval) who did not respond to a conventional prior invitation. The trial will assess the response to alternative invitation strategies and answer the question of whether experimental interventions including sending of self-sampling devices are more effective in generating greater participation in screening than sending conventional reminder letters. The trial will be conducted in different geographical areas to verify whether findings are reproducible in diverse regions.

The secondary objectives are to collect the barriers and levers that a self-sampling received at home can provide; to collect the barriers and levers to CC screening from health professionals [general practitioners (GPs), midwives and gynaecologists]; to assess compliance with gynaecological follow-up among women with a positive HPV test and to map the distribution of genotypes.

### Trial Design

The CapU4 study is a randomised controlled trial (1:1:1) with three arms with two experimental interventions and one control arm. Figure 1 illustrates the trial design and the SPIRIT checklist is detailed in Supplementary Material. Figure 2 summarises the timeline of the study.

**FIGURE 1 F1:**
[figure not shown]
Flow chart describing the study. The CapU4 protocol–France—2022–2024.

**FIGURE 2 F2:**
[figure not shown]
Timeline of study recruitment, HPV testing, gynaecological follow-up and semi-structured interviews/focus groups. The regional deployment of the national organized cervical cancer screening program began in Pays de la Loire in 2020. The sending of the 15,000 conventional letters associated or not with a self-sampling kit or a questionnaire will take place in March 2023. A first series of semi-structured interviews and exploratory focus groups was carried out in 2022. A second series took place in 2023. Samples will be collected until September 2023. Gynaecological follow-up of women (collection of cytological results of smears and histological results following a possible colposcopy) will continue until September 2024. The CapU4 protocol—France—2022–2024.

The three arms will be: 1) women receive a conventional invitation letter sent by post to the home address of eligible women recommending them to make an appointment to a doctor or a midwife for the collection of a cervical specimen; 2) eligible women receive at their home address an invitation letter with, in addition, a vaginal self-sampling kit; and 3) eligible women receive at their home address an invitation letter with, in addition, a urine collection kit. Half of the women will receive a questionnaire adapted according to the type of self-sampling or the control arm (Supplementary Material) after a sub-randomisation performed in each arm (Figure 1). A team of psychologists will investigate attitudes and experiences by semi-structured/focus-group interviews with voluntary CapU4 participants and with health professionals.

### Participants

The target population will be women aged between 30 and 65 years, living in the Departments of Mayenne, Sarthe and Vendée (Pays de la Loire, France) and who have not carried out a screening test (cytology of smear or HPV test) following a letter sent 12 months previously in 2021. Therefore, these are women whose last cervical sample was performed more than 4 years ago and who are reluctant to receive at least a first letter.

Non-inclusion criteria are: recent cervical sampling (less than 3 years old), women younger than 30 or older than 65 years, women who have had a hysterectomy, women with ongoing follow-up for a cervical lesion, women who are not members or beneficiaries of a social security system.

The target population will be defined by a query in the Centre Régional de Coordination de Dépistages des Cancers (CRCDC)—Pays de la Loire’s business software. CRCDC, which is a public health body governed by the French law on non-profit associations, provides colorectal, breast, and cervical cancer screenings in the Pays de la Loire region.

### Study Setting

The departments of Mayenne, Sarthe and Vendée were chosen because their participation rate for cervical smear screening is lower than the French national and the Pays de la Loire region average. These are rural territories known as medical desertification where access to care is limited due to low population density and larger distances to health services. The population of women aged between 30 and 65 years in Mayenne is 67,946, in Sarthe is 126,765, in Vendée is 157,050 and in Maine-et-Loire is 181,306 according to the French Public Health estimate for 2019. We will also be able to compare these three departments, in which organised screening is starting, with the Maine-et-Loire department which has been experimenting with this screening for 10 years.

### Interventions

The control arm corresponds to women receive a conventional invitation letter sent by post to the home address of eligible women recommending them to make an appointment to a doctor or a midwife for the collection of a cervical specimen. The two experimental interventions are: 1) eligible women receive at their home address a vaginal self-sampling kit (FLOQSwabs^®^ Copan Diagnostics, Brescia, Italy) in addition to the conventional invitation letter; and 2) eligible women receive at their home address a urine collection kit (Colli-Pee device, Novosanis, Wijnegem, Belgium) in addition to the conventional invitation letter.

With the conventional invitation letter, the women will receive an information brochure on the study (arms 2 and 3), a questionnaire (half of the population of the three arms), a self-sampling device with instruction (arms 2 and 3) and a prepaid return envelope. The women who will receive the self-sampling kit will place their prepaid return envelope in a post box.

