### Outcomes

#### Primary Outcomes

Participation rates (number of responding/number of invited) in each arm, difference and ratios of participation rates between the control and the two intervention arms.

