#### Attitudes and Acceptance by Women

A questionnaire will be sent to half of the population of the three arms to assess the reasons for not performing a cervical smear. The benefits of performing self-sampling will concern arms 2 and 3 with the self-samplings kits (see Supplementary Material).

Then, in order to understand the obstacles of the target population regarding screening, semi-structured interviews will be first conducted by psychologists [26, 27]. The interviews will be recruited among the women who performed the self-sampling and who have agreed to leave their contact information. A random draw based on socio-demographic and territorial characteristics will then be carried out to avoid the over-representation of certain populations. Special attention will be paid to the population characterised as under-screened (over 50 years old) and to vulnerable populations (economic precariousness because they benefit from complementary health care, medically desertified places, etc.). These interviews may be conducted face-to-face or remotely depending on the woman’s medical and geographical situation. The objective will be to determine the motivations of the woman who returned a self-sample, stopping on the cognitive path from the knowledge of the device to the pre-diagnosis and its consequences but also what they do with the result received. Indeed, the reception of a negative, unsatisfactory or positive result may not lead to a medical consultation, even though it would be recommended. The semi-directive interview will also allow gathering the experience of the sample collection process to measure satisfaction and assess the value given to the information received.

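### The primary contrast pools control women with and without a questionnaire, so it is unconfounded but measures the kits against the current letter only under conditions the plan leaves open

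*Protocol article*

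**What the plan says.** **Comparator.** The Objectives section sets out to evaluate the two self-sampling strategies and "compare them to the current invitation strategy in rural departments in France". Under Interventions, "The control arm corresponds to women receive a conventional invitation letter sent by post to the home address of eligible women", and the questionnaire is not part of that definition.

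**Mailing.** The next paragraph of Interventions lists the contents of the envelope: "the women will receive an information brochure on the study (arms 2 and 3), a questionnaire (half of the population of the three arms"). The Trial Design text after the Figure 2 legend says "Half of the women will receive a questionnaire adapted according to the type of self-sampling or the control arm", and that this happens "after a sub-randomisation performed in each arm". The section on attitudes and acceptance by women gives the purpose as "to assess the reasons for not performing a cervical smear" and adds that "The benefits of performing self-sampling will concern arms 2 and 3 with the self-samplings kits".

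**Analysis.** The primary outcome is the participation rate in each arm and the "difference and ratios of participation rates between the control and the two intervention arms". Neither that section nor Statistical Methods mentions questionnaire allocation in the arm contrast. Secondary Outcomes lists participation with versus without the questionnaire as a comparison to be made.

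**The concern.** The label, the mailing and the contrast do not line up. The label is the current letter. The control mailing is the letter alone for one half and the letter plus a questionnaire for the other. The contrast averages over the two halves without saying so. Asking a non-attender why she has not had a smear could act as a prompt, and the kit-arm version is not the same instrument. The plan itself treats an effect on participation as an open question, since it makes it a secondary outcome.

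What is at stake is the meaning of the headline result. The Discussion looks to regional and even national deployment and plans an extra cost per extra screened woman. That figure has the participation difference in its denominator. If the extra cost per invited woman is taken as fixed (an assumption), reading a 3-point gain as 2 points raises it by 3/2 − 1 = 50%, and reading it as 4 points lowers it by 1 − 3/4 = 25%.

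**Working it through.** **Inputs.** From Sample Size: control participation 12–14%, gain of 3–7 points, 95% confidence, 90% power, 5,000 women per arm. From Trial Design: questionnaire randomised to half of each arm, hence about 2,500 with and 2,500 without. The size of any questionnaire effect is not given; the range of −2 to +2 points below is an assumption.

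**1. The plan's own figure.** The two-sided two-proportion formula with continuity correction gives 588 per arm for 12% v 19% and 3,123 for 14% v 17%. Both match the stated range exactly.

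**2. What pooling estimates.** Let c and k be participation without the questionnaire in the control and a kit arm, and q_c and q_k the change it causes in each. With half of each arm exposed:

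- pooled control rate = c + q_c/2
- pooled difference = (k − c) + (q_k − q_c)/2
- pooled ratio = (k + q_k/2) / (c + q_c/2)

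So the control rate is the routine-letter rate only if q_c = 0. The difference is the routine-letter difference only if q_k = q_c. The ratio is preserved only if the effect is proportionally the same in both arms. When k differs from c, the difference and the ratio are both preserved only if the questionnaire does nothing.

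**3. Illustrations** (power at 5,000 per arm, two-sided 0.05, no continuity correction):

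| c v k | q_c, q_k (points) | Pooled rates | Difference | Ratio | Power |
|---|---|---|---|---|---|
| 12% v 15% | 0, 0 | 12% v 15% | 3.0 | 1.25 | 99.2% |
| 12% v 15% | +2, +2 | 13% v 16% | 3.0 | 1.23 | 98.9% |
| 12% v 15% | +1, 0 | 12.5% v 15% | 2.5 | 1.20 | 95.3% |
| 12% v 15% | +2, 0 | 13% v 15% | 2.0 | 1.15 | 82.2% |
| 14% v 17% | 0, 0 | 14% v 17% | 3.0 | 1.21 | 98.6% |
| 14% v 17% | +2, 0 | 15% v 17% | 2.0 | 1.13 | 77.9% |
| 14% v 17% | 0, −2 | 14% v 16% | 2.0 | 1.14 | 80.0% |
| 14% v 17% | 0, +2 | 14% v 18% | 4.0 | 1.29 | >99.9% |

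At a true 7-point gain, power stays above 99.9% for all shifts in this range.

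**4. The no-questionnaire stratum.** The 95% half-width is 1.96 × √[(p₁(1−p₁) + p₂(1−p₂))/n]. At 14% v 17% this is 1.96 × √(0.2615/2,500) = 2.0 points, against 1.96 × √(0.2615/5,000) = 1.4 points, wider by a factor of √2, or about 40%. Power at 2,500 per arm for 14% v 17%: (0.03 × 50 − 1.96 × √0.26195)/√0.2615 = 0.97, which is 83.4%. For 13% v 16% it is 85.4%, and for 12% v 15% it is 87.4%. With the continuity correction that the plan used, 90% power for a 3-point gain needs 2,791 to 3,123 per arm, more than the stratum holds. For a 4-point gain it needs 1,629 to 1,813, which the stratum covers.

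**5. Would the secondary questionnaire contrast settle it?** Over all arms (7,500 v 7,500) an average effect of about 1.8 to 2.0 points is detectable with 90% power, from 3.2416 × √(2p(1−p)/7,500) at p = 14% and 17%. A difference in effect between two arms uses four cells of 2,500, with standard error √[2(p₁(1−p₁) + p₂(1−p₂))/2,500] = 1.37 to 1.51 points, so 80% power starts at about 3.8 to 4.2 points. The average effect is reasonably well covered, but a 1–2 point difference between arms would probably be missed, and that is what moves the pooled difference.

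**The case against.** The strongest reply is that nothing here is biased. The questionnaire is a second randomised factor given to half of every arm, and averaging over it is the ordinary marginal analysis of a factorial-type layout. This stands. A reader might infer that the questionnaire confounds the kit comparison or spoils the control arm. The documents do not support that: exposure is balanced by design, and an equal effect in points leaves the difference untouched.

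Three further readings also go too far.

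- *The pooled gain is off by a point.* The 2.0 to 4.0 range comes from an assumed effect confined to one arm. No document supports its size or that confinement.
- *The questionnaire exists only in the trial.* Its research purpose and its random allocation make this likely, but the Introduction's account of the routine programme does not list what the mailing contains.
- *The brochure sent only with the kits is a second flaw.* The Objectives compare whole invitation strategies, and study information that travels with the kit is part of that strategy. It limits attribution to the kit alone and contradicts nothing.

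It can also be said that stratification is a matter for the analysis plan, which is not shown, and that the questionnaire halves are openly described. That is fair as to model detail. It does not cover the label: the article itself fixes the comparator's name, the mailing and the primary contrast, and the name fits only half of the control arm.

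**Conclusion.** The point holds in limited form. The arm contrast is valid for what was mailed, namely letter with kit and brochure against letter, each with a questionnaire in half the women. It is not automatically an estimate against the current letter. Reading it that way needs no questionnaire effect for the control rate, and the same effect in every arm for the difference; the plan leaves both open. If the effect is equal in points, the difference is unchanged and the ratio barely moves (1.25 to 1.23 in the example). If it is 2 points in one arm only, a 3-point gain is reported as 2 or 4. These shifts are assumptions chosen to show the scale. They matter mainly near the lower end of the plan's range; at a 7-point gain, power is unaffected although the estimate can still move by a point.

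A reader might conclude that the no-questionnaire women should become the primary analysis. Their 83–87% power for a 3-point gain falls short of the plan's 90%, so they are better used in support.

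**What to change.** 1. Keep the pooled contrast as primary, and state that it is stratified by or adjusted for questionnaire allocation. With equal allocation this will hardly change the estimated difference. It makes the averaging explicit but does not by itself give the routine-letter contrast.
2. Describe the control as *letter, half with questionnaire*, and the experimental arms as *letter plus kit plus study brochure*, half with questionnaire.
3. Beside the pooled result, report the rates, difference and ratio for each kit arm versus letter among women randomised to no questionnaire, labelled as the estimate against the current strategy.
4. Show that estimate as a sensitivity case in the cost-effectiveness analysis.

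The mailing and the sample size do not change, because the randomisation already provides the stratum. The cost is precision in the added estimate: about 2,500 women per arm, an interval about 40% wider, and power below 90% for a 3-point gain. It should therefore be presented as supporting evidence, with its interval, and not as a second test of the primary hypothesis.

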### Outcomes

#### Primary Outcomes

Participation rates (number of responding/number of invited) in each arm, difference and ratios of participation rates between the control and the two intervention arms.

